## Trial status

4

We estimate that this clinical study will last for 18 months, starting from July 2022 to February 2024. Patients will be recruited from multiple centers across Jiangsu Province. A total of 300 patients will be screened for this trial.

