**Methods/Design:**

This study is designed as a prospective, multicenter, randomized, controlled phase II study in patients histologically or cytologically diagnosed with GA/GEJA who underwent D2 gastrectomy and achieved R0 or R1 resection. From February 2022, a total of 300 stage III patients will be enrolled and subjected according to ctDNA sequencing results, and those with positive results will subsequently be randomized 1:1 to arm A or B. Patients in arm A will receive anlotinib, penpulimab and XELOX for 6-8 cycles, maintained with anlotinib and penpulimab for up to 1 year, while patients in arm B will receive XELOX alone for 6-8 cycles. ctDNA-negative patients will be assigned to arm C, and patients who are ctDNA positive but failed in randomization will be assigned to arm D. Patients in arms C and D will receive the investigator’s choice of therapy. The primary endpoint is the median disease-free survival (DFS) of arm A versus arm B determined via CT/MRI imaging. Secondary endpoints include the DFS of ctDNA positive patients versus ctDNA negative patients, the 2- and 3-year DFS rates, overall survival (OS), the impact of hallmark molecules on the treatment response, adverse events (AEs), and the impact of nutrition status or exercise on recurrence.

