### Trial design

2.2

This study was designed as a prospective, multicenter, randomized, controlled, open-label and multicenter phase II clinical trial conducted in China. beginning in June 2022. Patients in arm A (experiment group) will undergo XELOX chemotherapy combined with anlotinib and penpulimab until they reach the 6-8 cycle without recurrence. Subsequently, they will receive anlotinib combined with penpulimab as maintenance therapy until recurrence or death occurs or reach the maximum length of 1 year. Patients in arm B (control group) will undergo XELOX chemotherapy for 6-8 cycles. Arm C&D will receive the researcher’s choice of treatment according to recommendations by the Chinese Society of Clinical Oncology (CSCO) guidelines. All ctDNA positive patients should receive ctDNA tests every 3 months as a dynamic monitoring procedure. Considering that NGS analysis may take up to 10 working days, patients could receive 1 cycle of XELOX chemotherapy after ctDNA sampling. Follow-ups and evaluations will be carried out regularly. In addition to data concerning treatment and recurrence, data on nutritional and exercise habits will also be collected in an exploratory attempt to determine the impact of nutrition and exercise on survival and the risk of recurrence.

The primary endpoint of our trial is the DFS of ctDNA-positive patients receiving XELOX combined with anlotinib and penpulimab versus ctDNA-positive patients receiving XELOX alone (arm A versus arm B). The secondary endpoints include the DFS of ctDNA-positive patients versus ctDNA-negative patients, the 2-year DFS rate, the 3-year DFS rate, overall survival (OS), the relationship of dynamic ctDNA status and treatment response, adverse events (AEs), and the impact of nutrition status and exercise on recurrence.

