### Statistical analysis

2.6

Previous research reported that the median DFS of postoperative adjuvant chemotherapy in ctDNA-positive GA/GEJA patients is approximately 12 months (13, 14). Our hypothesis is that anlotinib plus penpulimab combined with XELOX will prolong DFS to 24 months. Setting the single-sided α as 0.05, β as 0.2, the length of in-group time as 18 months and the length of follow-up as 24 months, the calculated sample size is 36 patients for the test group (arm A) and 36 patients for the control group (arm B); presuming that the drop-off rate is 10%, the total number of participants needed is 40 each group. The key secondary endpoint is the difference in DFS between ctDNA-positive and ctDNA-negative patients treated by only chemotherapy. Given that the median DFS of ctDNA-negative patients receiving standard treatment is approximately 36 months, two-sided α = 0.05, β = 0.2, the length of in-group time is 18 months, and the length of follow-up is 36 months, the sample size should be 14 each for the ctDNA-positive group and the ctDNA-negative group. Taking both hypotheses into consideration, we presume at least 80 ctDNA-positive patients would be needed to complete this study. Considering that the positive rate of ctDNA in postoperative GA/GEJA patients is approximately 25-30%, a total of 300 participants needs to be screened.

Statistical analysis will be carried out by statistics specialists who will take part in the study during the whole process, from the study design and implementation to the data analysis phase. Measurement variables will be analyzed by means of *t test*, paired *t test*, rank-sum test, paired rank-sum test, analysis of variance (ANOVA), etc. Count variables will be analyzed using the Cochran–Mantel–Haenszel (CMH) chi-squared test, logistic regression and Fisher’s exact test. Ordinal variables will be analyzed via the rank-sum test. Survival data will be compared via the Kaplan–Meier method or Cox regression. The main clinical response indicators will be subjected to per-protocol population (PP) and full analysis set (FAS) analyses simultaneously. A two-sided test for significance was performed as the default, and *P<*0.05 was considered significant. The analysis will be performed using SAS software. The data analysis is planned to be at mid-term and upon completion of this trial.

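### The stated study length of 18 months to February 2024 contradicts the 42 and 54 months that the sample sizes assume, and the start date is given three ways

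*Protocol article*

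**What the plan says.** Section 4 (Trial status) gives the duration of the whole study: "We estimate that this clinical study will last for 18 months, starting from July 2022 to February 2024".

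Section 2.6 (Statistical analysis) sizes the primary comparison of arms A and B with "the length of in-group time as 18 months and the length of follow-up as 24 months", and the key secondary comparison of ctDNA-positive with ctDNA-negative patients with "the length of in-group time is 18 months, and the length of follow-up is 36 months". It places the analyses at mid-term and at completion of the trial, without a date or an event count.

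The abstract (Methods/Design) starts enrolment earlier: "From February 2022, a total of 300 stage III patients will be enrolled". Section 2.2 (Trial design) has the trial beginning in June 2022, and lists among the secondary endpoints "the 2-year DFS rate, the 3-year DFS rate, overall survival (OS".

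**The concern.** A study that lasts 18 months cannot contain 18 months of accrual followed by 24 or 36 months of follow-up. Because the final analysis is tied to completion of the trial, and section 4 gives the only calendar date for completion, someone planning the data cut-off could take February 2024 as that date. The primary comparison would then be made on far fewer events than the sample size assumes. The 2- and 3-year DFS rates would have little or no follow-up behind them. The three start dates leave even the length of the stated period uncertain.

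**Working it through.** **Inputs, all from section 2.6.** In arm B, "median DFS of postoperative adjuvant chemotherapy in ctDNA-positive GA/GEJA patients is approximately 12 months". The hypothesis is that "anlotinib plus penpulimab combined with XELOX will prolong DFS to 24 months". Under exponential DFS this is a hazard ratio of 12/24 = 0.5. The error rates and times are given as "Setting the single-sided α as 0.05, β as 0.2, the length of in-group time as 18 months and the length of follow-up as 24 months". Stated result: 36 per arm, or 40 with 10% dropout. I assume exponential DFS and uniform accrual.

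**Step 1: events needed (Schoenfeld, 1:1).** d = 4(z₀.₉₅ + z₀.₈₀)² / (ln HR)² = 4(1.645 + 0.842)² / (0.693)² ≈ 51.5, so 52 events.

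**Step 2: which schedule gives 36 per arm?** With accrual A, analysis at month T and λ = ln 2 / median, the probability of an event is p = 1 − [exp(−λ(T−A)) − exp(−λT)] / (λA). The number per arm is 52 / (p_B + p_A).

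- 24 months after the last entry (A = 18, T = 42): p_B = 0.845, p_A = 0.610; 52/1.4547 = 35.75, so 36. Then 36/0.9 = 40. Both stated figures are reproduced.
- 24 months for each patient: p_B = 0.75, p_A = 0.50; 52/1.25 = 41.6, so 42.
- 24 months in total (A = 18, T = 24): p_B = 0.560, p_A = 0.344; 52/0.9047 = 57.5, so 58.

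Other standard formulas (Freedman, Lachin-Foulkes) give 38 to 39 at month 42 and 61 to 62 at month 24, so they point to the same schedule. The primary therefore rests on 18 + 24 = 42 months. By the same construction the key secondary rests on 18 + 36 = 54 months.

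**Step 3: the dates.** July 2022 to February 2024 is 19 months from the start of one month to the start of the other, or 20 if both months count in full. From February 2022 to February 2024 is 24 months.

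**Step 4: the primary comparison if analysed at the stated end.** Expected events are 36(p_B + p_A). Power is Φ(½√d·|ln 0.5| − z), with z = 1.645 one-sided and 1.960 two-sided. The two-sided figure is shown because section 2.6 names a two-sided test as its default.

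| Analysis month (accrual 18, N = 72) | Events | Share of 52 | Power, one-sided 0.05 | Power, two-sided 0.05 |
|---|---|---|---|---|
| 18 | 21.5 | 41% | 49% | 36% |
| 19 | 23.6 | 45% | 51% | 39% |
| 20 | 25.6 | 49% | 54% | 42% |
| 24 (February 2022 start) | 32.6 | 63% | 63% | 51% |
| 42 (section 2.6) | 52.4 | 101% | 81% | 71% |

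Check at month 18: p_B = 0.378 and p_A = 0.220, so 36 × 0.598 = 21.5 events; ½ × √21.5 × 0.693 − 1.645 ≈ −0.04, so power is 49%.

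If all 80 patients contribute without loss, months 18 to 20 give 23.9 to 28.4 events and one-sided power of 52% to 58%. If accrual is spread over the full 20 months, 72 patients give 23.3 events and 51%.

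**Step 5: follow-up for the landmark rates.** From a June or July 2022 start, nobody reaches 24 months by February 2024. From a February 2022 start, only the earliest entrants could. Under any of the three starts nobody reaches 36 months.

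**The case against.** The strongest reply is that section 4 simply mislabels the recruitment period. Its 18 months equals the accrual time in section 2.6, and its other two sentences are about recruitment and screening. A literal 18-month study would also clash with the follow-up in section 2.6, the 2- and 3-year DFS rates, arm A maintenance for up to 1 year, and survival follow-up after treatment. I accept this as the likeliest explanation, and on that reading no events or power are lost. It does not remove the error: nothing in the article says that February 2024 is only the end of recruitment.

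Four stronger readings are tempting and are not supported.

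- A reader might infer that the trial is underpowered by design. That holds only if the final analysis is done in February 2024, and section 2.6 gives no date for it.
- A reader might infer that half the power is lost. About half the events would be missing, but one-sided power of 49% to 54% is 61% to 68% of the planned 80%. It comes near half of 80% only on the two-sided test, for which the 80% was not planned.
- A reader might infer a similar loss for the key secondary. With only the 14 per group of section 2.6, two-sided power at months 18 to 20 would be 32% to 37%. If all enrolled patients were used, assuming 40 in arm B and 300 − 80 = 220 ctDNA-negative, it would be about 79% to 86%. The documents do not establish a loss there.
- A reader might infer that no patient could contribute to a 2-year DFS rate. That depends on which start date is right.

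It is also fair to say that an event-driven cut-off is one option among several, and that cut-off rules are commonly left to the full protocol or the analysis plan. The point here is the contradiction between stated durations, not a missing rule.

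**Conclusion.** The duration in section 4 is wrong as written. It gives the whole study 18 months, over dates that span 19 to 20, while section 2.6 needs 42 months for the primary and 54 for the key secondary. The start dates in the abstract, section 2.2 and section 4 also disagree. Most probably this is a labelling error for the recruitment period.

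Its size is conditional. If the final analysis really took place at the stated end, the primary would have about 22 to 26 of 52 events and one-sided power of about 49% to 54% (36% to 42% two-sided) instead of 80%, or about 33 events and 63% from a February 2022 start. Few or no patients would have 2 years of follow-up and none would have 3. These figures rest on exponential DFS, uniform accrual over 18 months and 72 evaluable patients. Under the first two assumptions the plan's own 36 per arm is reproduced. The contradiction itself rests on no assumption.

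**What to change.** Reconcile the abstract, section 2.2, section 2.6 and section 4:

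- Give one start date throughout, and make the length of the period agree with its dates.
- Label the period to February 2024 as recruitment, if that is what is meant.
- State that the primary analysis takes place 24 months after the last randomisation, when about 52 DFS events in arms A and B together are expected. With the last randomisation in February 2024, this is about February 2026.
- State that the key secondary and the 3-year DFS analysis take place 36 months after the last entry, about February 2027 on the same basis.

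An event-driven cut-off at 52 events would also serve, but is not required.

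If February 2024 really is the end of the study, keep the date, restate the primary power as about 50%, and say what can still be reported for the 2- and 3-year DFS rates.

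The cost is wording only. The follow-up is already assumed in section 2.6, so no patients or visits are added to what the sample size presumes.

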## Ethics statement

The studies involving humans were approved by the ethics committee of the First Affiliated Hospital of Nanjing Medical University. The studies were conducted in accordance with the local legislation and institutional requirements. The participants provided their written informed consent to participate in this study.
